# Regular pulse checks for patients with non-cardioembolic stroke in rehabilitation hospitals to improve recognition and detection of atrial fibrillation (the ESCORT study): protocol for a prospective multicenter observational study

**DOI:** 10.3389/fneur.2023.1247020

**Published:** 2023-08-16

**Keywords:** cryptogenic stroke, paroxysmal atrial fibrillation, protocol, rehabilitation, pulse check

## Abstract

**Background:**

Cryptogenic stroke (CS) are heterogeneous in origin; however, most CS are embolic mechanism. Paroxysmal atrial fibrillation (AF) is suspected to be a major type of CS that leads to severe cerebral infarction without anticoagulant use. Therefore, the identification of AF is vital in patients with CS. However, patients are often unaware of AF because they have no symptoms, and AF may not be detected on an electrocardiogram (ECG) or Holter ECG on admission. After patients with stroke are treated in the acute phase, they are promptly transferred to a rehabilitation hospital for functional recovery. Once the patient is transferred to a hospital, a few attempts are made to detect AF. In addition, rehabilitation therapists are considered to have insufficient awareness of the possibility of undiagnosed AF.

**Objective:**

This study aimed to increase the understanding of the importance of AF detection in patients with ischemic stroke among therapists in rehabilitation hospitals and to investigate whether regular pulse screening can aid in the detection of AF. If AF was detected, we determined the rate and timing of AF detection and identified the patient characteristics.

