**Methods:**

This multicenter prospective observational study aimed to detect AF in patients with non-cardiac stroke at rehabilitation hospitals. Therapists performed pulse checks before, during, and after rehabilitation. If arrhythmia or tachycardia was detected, an ECG was performed, and the physician checked for AF. If the patient complained of chest symptoms, electrocardiography (ECG) was performed to check for AF. We investigated the characteristics, laboratory data, cognitive status, complications, such as stroke recurrence, and functional outcomes of patients with AF.

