## Introduction

1.

Approximately 15%–40% of all ischemic strokes are characterized as cryptogenic stroke (CS) (1). CS are heterogeneous in origin; however, many CS are thought to exhibit embolic mechanisms. Paroxysmal atrial fibrillation (AF) is suspected to be the major cause of CS. AF attributable to large- or small-vessel disease has also been reported in stroke patients (2).

The number of patients with AF increases with age (3, 4); however, AF is sometimes difficult to detect. AF is classified as persistent AF if it lasts for more than 1 week or as paroxysmal AF if it disappears within 1 week. Paroxysmal AF is sometimes unrecognized by patients because it is asymptomatic (5) and may not be detected on electrocardiography (ECG) or Holter ECG examination on admission.

Paroxysmal and persistent AF are associated with a high risk of recurrence without anticoagulant therapy (6); therefore, we treated the patients with anticoagulant therapy to prevent stroke due to AF. Current Japanese guidelines for stroke recommend that stroke in which AF is not detected should be classified as non-cardiogenic stroke and treated with antiplatelet agents (aspirin, clopidogrel, prasgrel, and cilostazol) to prevent recurrence. However, when atrial fibrillation is observed, antiplatelet drugs are insufficient to prevent stroke recurrence, and anticoagulants (warfarin, dabigatran, rivaroxaban, apixaban, edoxaban) are more effective in preventing recurrence (7, 8). Therefore, it is important to actively identify patients with stroke without AF.

Recently, stroke care has changed considerably with advances in acute therapy and shortened length of hospitalization. Once patients are transferred to a rehabilitation hospital, fewer attempts are made to detect AF. In addition, rehabilitation therapists have insufficient awareness of the possibility of undiagnosed AF and the importance of AF detection. In this study, we aimed to increase the understanding of the importance of AF detection among therapists in rehabilitation hospitals and investigate whether regular pulse screening can aid in the detection of AF. If the feasibility and usefulness of regular pulse testing during rehabilitation are confirmed, the detection of AF after stroke can be recommended.

This study also aimed to clarify the rate and timing of AF detection by performing pulse testing.

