### Study design

2.1.

The regular pulse check for patients with non-cardioembolic stroke in a rehabilitation hospital to improve recognition and detection of atrial fibrillation (ESCORT) study is an observational, multicenter, prospective registry of patients diagnosed with ischemic stroke.

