### Evaluations and follow-up

2.4.

The following parameters were evaluated: (1) feasibility of pulse checks in rehabilitation hospitals, (2) proportion of AF detection, and (3) proportion of initiation of anticoagulant therapy. Patients usually undergo rehabilitation therapy 3 times daily at rehabilitation hospitals. Trained rehabilitation staff performed pulse checks for each patient before, during, and after rehabilitation (9 times daily). If an irregular pulse and tachycardia (heart rate of 120 beats/min or faster) were detected, a 12-lead ECG immediately (within 5 min) after pulse assessment was essential to confirm or rule out AF (Figure 1). For patients with identified AF, the prescription will be changed to an anticoagulant at the rehabilitation hospital and the study office will be contacted. If the attending physician at the rehabilitation hospital has concerns about the prescription, the study office will consult about the prescription. The duration of the regular pulse monitoring is all periods from obtaining consent to admission in rehabilitation hospital.

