### Sample size

2.6.

Notably, this study has not been previously reported. The number of possible participants in the study in a year was calculated from the number of admissions at participating facilities in the previous year and set at 1000.

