### Data analysis plan

2.7.

We will examine the proportion of patients with AF detected, timing of detection, and characteristics of patients with AF. Clinical characteristics such as sex, age, laboratory data, echocardiography data, and brain imaging data, and outcomes will be compared between the patients in the AF and non-AF group. Sub-group analyses will be planned for patients who used other long-term electrocardiographic monitors, such as ICM. All statistical analyses will be performed using the SPSS software (version 27; SPSS Japan, Inc., Tokyo, Japan). The results will be considered statistically significant at *p* < 0.05. Univariate analyses will be performed using *χ*^2^ and Mann–Whitney *U* tests, as appropriate. Data will be presented as medians and interquartile ranges. Categorical variables will be presented as frequencies and percentages.

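### The single-arm design can estimate AF yield under regular pulse checks, but not whether the checks add detection, so the objective and conclusion should be worded as a yield estimate

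*Protocol article*

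**What the plan says.** The Objective in the Abstract is "to investigate whether regular pulse screening can aid in the detection of AF", and the Introduction repeats it. The title likewise presents the checks as a means of improving AF detection. The Introduction says that AF detection can be recommended if feasibility and usefulness are confirmed. The Discussion carries confirmed usefulness forward to prevention of stroke, heart failure and death.

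Section 2.1 says that the study "is an observational, multicenter, prospective registry of patients diagnosed with ischemic stroke". Under section 2.4, "Trained rehabilitation staff performed pulse checks for each patient before, during, and after rehabilitation (9 times daily". The parameters listed there are "1) feasibility of pulse checks in rehabilitation hospitals, (2) proportion of AF detection, and (3) proportion of initiation of anticoagulant therapy".

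Section 2.6 sets the target of 1000 from a number of possible participants "calculated from the number of admissions at participating facilities in the previous year". In section 2.7, "We will examine the proportion of patients with AF detected, timing of detection, and characteristics of patients with AF". The contrasts named there are AF against non-AF patients, and subgroup analyses of patients with an ICM or another long-term monitor.

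Detection without scheduled checks is described only in words: "Once patients are transferred to a rehabilitation hospital, fewer attempts are made to detect AF".

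**The concern.** To say that screening aids or improves detection is to say that more AF is found, or found earlier, than would be found without it. That needs two quantities: detection with the checks and detection without them. The design supplies the first only.

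The missing quantity is not shown to be zero. The Introduction speaks of fewer attempts at detection, not none. Within the study there are routes to AF that do not depend on a pulse check. The Abstract states: "If the patient complained of chest symptoms, electrocardiography (ECG) was performed to check for AF". Section 2.3 also admits patients with an ICM. The article does not say that the proportion detected will be split by route.

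At stake is the conclusion. Neither the Introduction nor the Discussion says what would count as confirmation, so a crude yield could be taken as showing that the checks are useful even where part or all of it would have been found anyway.

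**Working it through.** **Inputs from the article.** n = 1000 (section 2.6). All patients are checked (section 2.4). The usual-care detection rate p0 is not given, and neither is an expected yield.

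**The plan's own figure.** The 1000 is a head-count from admissions. No admission numbers, expected rate, precision target or power are shown, so no formula can reproduce or contradict it.

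**Step 1: what the objective needs.** The added detection is Δ = p1 − p0, where p1 is the proportion detected with pulse checks in place. The registry estimates p1. The AF against non-AF contrast describes who has AF and gives no p0. The ICM subgroup gives none either, because those patients are pulse-checked too. It could inform the sensitivity of the checks, but not the usual-care yield.

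**Step 2: what the study can give.** Assume 30 cases in 1000. The Wilson 95% interval, with z = 1.96 and z² = 3.84, is:

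- centre: (0.030 + 3.84/2000) / (1 + 3.84/1000) = 0.03192/1.00384 = 0.0318
- half-width: 1.96 × √(0.030 × 0.970/1000 + 3.84/(4 × 1000²)) / 1.00384 = 0.0107
- interval: 2.1% to 4.3% (exact binomial: 2.0% to 4.3%)

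This is a reasonably precise estimate of yield.

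**Step 3: what it cannot give.** With the same 3.0% and assumed values of p0:

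| Assumed p0 | Δ (percentage points) |
|---|---|
| 0.5% | 3.0 − 0.5 = 2.5 |
| 1% | 3.0 − 1.0 = 2.0 |
| 3% | 3.0 − 3.0 = 0 |

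The reported result is identical in all three rows.

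**Step 4: a non-zero yield is not evidence of gain.** If the checks added nothing, P(at least one case) = 1 − (1 − p0)^1000. This is 99.3% at p0 = 0.5% and more than 99.99% at p0 from 1% to 5%.

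**Step 5: a benchmark would decide the reading.** For an exact one-sided binomial test at no more than 0.025, the smallest number of cases in 1000 that exceeds the benchmark is:

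| Assumed benchmark p0 | Cases needed |
|---|---|
| 1% | 18 |
| 2% | 30 |
| 3% | 42 |
| 5% | 65 |

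Thirty cases would clear 1%, just reach the threshold for 2%, and fall short for 3% and 5%. The article names no benchmark, so the reading is open.

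**Step 6: composition of the yield.** The total count can combine pulse-triggered, symptom-triggered and monitor-detected AF. The crude proportion is therefore not clearly the yield of the pulse checks themselves.

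**The case against.** The best defence is that the study is descriptive in practice. The Objective goes on to rate, timing and patient characteristics. Section 2.4 lists feasibility and two proportions, and section 2.7 plans proportions, timing and characteristics. The Discussion ties usefulness to detecting AF and starting anticoagulation, both of which are measured. If aiding detection only means that the checks find AF not previously known, a single-arm yield answers it. This stands for feasibility, rate, timing and characteristics, which need no comparator. It does not dispose of the title's language of improvement or of the recommendation that hangs on usefulness.

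Two stronger readings are tempting, and the article does not support them:

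- A reader might infer that the plan would treat any yield as confirming usefulness. Both statements about usefulness are conditional and no success rule is given. The text leaves that reading open but does not adopt it.
- A reader might infer from section 2.6 that an unscreened comparison cohort from the previous year is available and merely unused. The section documents an admission count. It does not say that eligible patients were identified, that their AF status can be retrieved, or that they had no pulse checks.

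It is also fair to say that zero gain sits poorly with the article's account of sparse detection efforts. That account makes a low p0 plausible but does not put a number on it.

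An analysis plan not shown here could add detail, but it could not create unscreened patients whom the described design does not collect.

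**Conclusion.** The concern holds in a limited form. The stated question is comparative in wording, every patient receives the checks, and the article gives no comparator, usual-care rate or benchmark. The study supports statements about AF yield, timing and feasibility under regular pulse checks. It does not support a statement that the checks increase detection, and a crude yield could be misread as one.

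The size cannot be fixed from the article. The range of 0 to 2.5 percentage points for an identical 3.0% result rests on an assumed yield and three assumed usual-care rates. It shows only that the result cannot tell these cases apart. The single-arm design itself is not a fault for the descriptive aims; the mismatch is between the design and the wording of the objective and conclusion.

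**What to change.** Restate the objective, and the conclusion to be drawn, as estimating the AF yield with a 95% CI during regular pulse checks in rehabilitation hospitals, alongside feasibility and timing. Drop the wording about whether screening can aid detection, and about confirming usefulness, wherever it would be read as a conclusion on added detection. This needs no new patients, procedures or data. Since the article appeared in August 2023, the month in which recruitment was due to end, the rewording should be declared openly in the report.

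Two additions are optional:

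- If the trigger for each diagnostic ECG is recorded, report the yield by route (pulse check, symptoms, ICM). This clarifies the yield but still does not measure the gain, because a case found by pulse check might later have been found by another route.
- A historical chart comparison could be supportive at most. It would need chart extraction at the six institutions and an ethics amendment, and the availability of a suitable cohort would have to be established first. Past charts would probably under-record AF, given the article's own account of few attempts at detection. The past patients would not be selected by consent, and practice may have changed over time.

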**Methods:**

This multicenter prospective observational study aimed to detect AF in patients with non-cardiac stroke at rehabilitation hospitals. Therapists performed pulse checks before, during, and after rehabilitation. If arrhythmia or tachycardia was detected, an ECG was performed, and the physician checked for AF. If the patient complained of chest symptoms, electrocardiography (ECG) was performed to check for AF. We investigated the characteristics, laboratory data, cognitive status, complications, such as stroke recurrence, and functional outcomes of patients with AF.

**Results:**

The study is in the enrollment phase. Recruitment began in September 2022 and will end in August 2023. Patients have provided written informed consent. The main results have been submitted for publication in your journal.

**Conclusion:**

The findings of this study will help identify patients with AF in rehabilitation hospitals and improve awareness among therapists.

## Introduction

1.

Approximately 15%–40% of all ischemic strokes are characterized as cryptogenic stroke (CS) (1). CS are heterogeneous in origin; however, many CS are thought to exhibit embolic mechanisms. Paroxysmal atrial fibrillation (AF) is suspected to be the major cause of CS. AF attributable to large- or small-vessel disease has also been reported in stroke patients (2).

The number of patients with AF increases with age (3, 4); however, AF is sometimes difficult to detect. AF is classified as persistent AF if it lasts for more than 1 week or as paroxysmal AF if it disappears within 1 week. Paroxysmal AF is sometimes unrecognized by patients because it is asymptomatic (5) and may not be detected on electrocardiography (ECG) or Holter ECG examination on admission.

Paroxysmal and persistent AF are associated with a high risk of recurrence without anticoagulant therapy (6); therefore, we treated the patients with anticoagulant therapy to prevent stroke due to AF. Current Japanese guidelines for stroke recommend that stroke in which AF is not detected should be classified as non-cardiogenic stroke and treated with antiplatelet agents (aspirin, clopidogrel, prasgrel, and cilostazol) to prevent recurrence. However, when atrial fibrillation is observed, antiplatelet drugs are insufficient to prevent stroke recurrence, and anticoagulants (warfarin, dabigatran, rivaroxaban, apixaban, edoxaban) are more effective in preventing recurrence (7, 8). Therefore, it is important to actively identify patients with stroke without AF.

Recently, stroke care has changed considerably with advances in acute therapy and shortened length of hospitalization. Once patients are transferred to a rehabilitation hospital, fewer attempts are made to detect AF. In addition, rehabilitation therapists have insufficient awareness of the possibility of undiagnosed AF and the importance of AF detection. In this study, we aimed to increase the understanding of the importance of AF detection among therapists in rehabilitation hospitals and investigate whether regular pulse screening can aid in the detection of AF. If the feasibility and usefulness of regular pulse testing during rehabilitation are confirmed, the detection of AF after stroke can be recommended.

This study also aimed to clarify the rate and timing of AF detection by performing pulse testing.

## Methods

2.

### Study design

2.1.

The regular pulse check for patients with non-cardioembolic stroke in a rehabilitation hospital to improve recognition and detection of atrial fibrillation (ESCORT) study is an observational, multicenter, prospective registry of patients diagnosed with ischemic stroke.

### Ethics approval

2.2.

Ethical approval for this study was obtained from the ethics committee of Nippon Medical School (A-2021-067) and the relevant ethics committees of all participating centers.

Written informed consent was obtained from all the patients or their family members before participating in the study. This study was registered with University Hospital Medical Information.

Network (UMIN) Clinical Trial Registry (UMIN000048536).

### Patient population

2.3.

Patient enrollment for this ongoing study began in September 2022 at six medical partner institutions in Tokyo, Japan. The inclusion criteria were as follows: (1) patients diagnosed with non-cardiogenic stroke, (2) patients aged >20 years, and (3) patients or their families who agreed to participate in the study and provided informed consent. Patients with insertable cardiac monitor (ICM) were also participated if they met the inclusion criteria. The exclusion criteria were as follows: (1) patients who are currently participating or will participate in another intervention trial, (2) patients with AF or atrial flutter, (3) patients diagnosed with less than 1 year to live, and (4) patients judged by their doctor to be ineligible to participate in the study. A full description of the inclusion and exclusion criteria is presented in Table 1. Trained stroke rehabilitation nurses and physicians educated the registered patients on pulse palpation according to a standardized protocol that focuses on evaluating the heart rate and rhythm regularity. First, rehabilitation therapists were educated about the health implications of AF (i.e., the risk of ischemic stroke, thromboembolism, heart failure, and mortality), clinical presentation, and its frequent asymptomatic nature. The potential health benefits of the intervention were also explained.

**Table 1 tab1:** Inclusion and exclusion criteria.

**Inclusion criteria**
Patients who have been diagnosed with non-cardiogenic stroke
Patients aged over 20 years
Patients or their family agreed in writing
**Exclusion criteria**
Patient is currently participating or will participate in another intervention trial
Patient has AF or atrial flutter
Patient diagnosed with less than 1 year to live
Patients judged by their doctor to be ineligible to participate in the study

### Evaluations and follow-up

2.4.

The following parameters were evaluated: (1) feasibility of pulse checks in rehabilitation hospitals, (2) proportion of AF detection, and (3) proportion of initiation of anticoagulant therapy. Patients usually undergo rehabilitation therapy 3 times daily at rehabilitation hospitals. Trained rehabilitation staff performed pulse checks for each patient before, during, and after rehabilitation (9 times daily). If an irregular pulse and tachycardia (heart rate of 120 beats/min or faster) were detected, a 12-lead ECG immediately (within 5 min) after pulse assessment was essential to confirm or rule out AF (Figure 1). For patients with identified AF, the prescription will be changed to an anticoagulant at the rehabilitation hospital and the study office will be contacted. If the attending physician at the rehabilitation hospital has concerns about the prescription, the study office will consult about the prescription. The duration of the regular pulse monitoring is all periods from obtaining consent to admission in rehabilitation hospital.

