**Figure 1 fig1:**
[figure not shown]
Study flowchart. This flowchart illustrates the design of this study. It shows the flow chart from stroke diagnosis at the stroke center to pulse and AF diagnosis at the rehabilitation hospital. AF, atrial fibrillation.

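### The Abstract and section 2.4 differ on whether an ECG is required for an irregular pulse below 120 beats/min and for a regular pulse at or above 120 beats/min

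*Protocol article*

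**What the plan says.** The protocol article states the rule that leads from a pulse check to an ECG in two places.

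- Abstract, Methods: "If arrhythmia or tachycardia was detected, an ECG was performed, and the physician checked for AF". No rate defines tachycardia here. A second trigger follows: "If the patient complained of chest symptoms, electrocardiography (ECG) was performed to check for AF".
- Section 2.4, Evaluations and follow-up: "If an irregular pulse and tachycardia (heart rate of 120 beats/min or faster) were detected, a 12-lead ECG immediately". The sentence goes on to set a limit of 5 minutes after the pulse assessment, calls this ECG essential to confirm or exclude AF, and cites Figure 1. Chest symptoms are not mentioned in this section.

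Section 2.4 also ties treatment to the result: "For patients with identified AF, the prescription will be changed to an anticoagulant at the rehabilitation hospital". Section 2.7 names what will be analysed: "We will examine the proportion of patients with AF detected, timing of detection, and characteristics of patients with AF". It then plans a comparison of patients with and without AF.

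**The concern.** The pulse check is the screening step of this study and the ECG is the confirming step. The trigger between them therefore governs which pulse findings must be followed up. One text makes either abnormal feature sufficient; the other, read literally, needs both at once.

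The finding that matters most is an irregular pulse at a rate below 120 beats/min. Under the literal *and*, AF presenting in this way carries no required ECG. If it stayed unconfirmed, three things could follow:

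- The patient would sit in the non-AF group of the section 2.7 comparison.
- The proportion with AF detected, one of the three evaluations in section 2.4, would be lower.
- The change to an anticoagulant, which depends on identified AF, could be delayed.

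The chest-symptom trigger in the Abstract cannot be relied on to recover all such cases. The Discussion itself says that AF in these patients is often without symptoms and unlikely to be found by symptom-driven monitoring.

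**Working it through.** The plan gives no figure to reproduce. The check sets the two rules side by side.

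**Inputs.** The pulse check assesses two features (section 2.3: a "standardized protocol that focuses on evaluating the heart rate and rhythm regularity"), so there are 2 × 2 = 4 possible findings. The rate threshold of 120 beats/min comes from section 2.4.

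**Assumptions.** Arrhythmia in the Abstract means an irregular pulse, and tachycardia in the Abstract uses the same 120 beats/min.

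| Pulse finding | ECG required, Abstract (*or*) | ECG required, section 2.4 (literal *and*) | Agree? |
|---|---|---|---|
| Irregular, 120 or faster | yes | yes | yes |
| Irregular, below 120 | yes | no | no |
| Regular, 120 or faster | yes | no | no |
| Regular, below 120 | no | no | yes |

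**Result.** The rules agree on 2 of 4 findings and differ on 2 of 4. If section 2.4 used *or*, they would agree on 4 of 4.

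**Direction.** Every finding that triggers an ECG under *and* also triggers one under *or*, but not the reverse. With everything else equal, the literal *and* can therefore only leave the number of required ECGs, and so the AF found through them, the same or lower.

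**Sensitivity to the threshold assumption.** The Abstract gives no rate. The difference for an irregular pulse below 120 does not depend on it, because in the Abstract irregularity alone is enough. If the Abstract meant a cut-off below 120, the wordings would also differ for a regular pulse between that cut-off and 120.

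**What the count does not show.** It counts logical combinations, not pulse checks or patients. The article gives no frequency of the four findings and no distribution of heart rate in AF, so no effect on the AF proportion can be calculated.

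**The case against.** The strongest reply is that the *and* in section 2.4 is a slip for a list of two separate triggers. Section 2.3 presents rate and rhythm as separate features, and the Abstract separates them with *or*. A screen for AF that is often silent and intermittent would more naturally be sensitive than limited to fast irregular pulses. The English is loose elsewhere, for instance "Patients with insertable cardiac monitor (ICM) were also participated if they met the inclusion criteria". Section 2.4 also cites Figure 1 for this very step; its caption says "It shows the flow chart from stroke diagnosis at the stroke center to pulse and AF diagnosis at the rehabilitation hospital", but the figure itself is not available here and may show the intended rule.

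Much of this stands. The loose-wording reading is plausible, and nothing in the article shows that any site withheld an ECG. But section 2.4 is the operative rule in the Methods and the only place with the threshold and the time limit, so anyone interpreting or repeating the study would use it. No visible text reconciles it with the Abstract. Even if Figure 1 shows *or*, the sentence that cites it would still need correcting.

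A reader might infer that the two texts give opposite instructions. They do not: section 2.4 says when an ECG is essential and is silent on the other findings. The contrast is between required and not required, and a discretionary ECG remains possible.

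A reader might also infer that the AF proportion is biased. That needs evidence that staff followed the literal *and*, and the article offers none. AF found through chest symptoms, an insertable monitor or a discretionary ECG is unaffected. Pulses are also taken 9 times daily, so AF passed over at a slower rate on one check could still be caught on another. The net effect could be small.

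**Conclusion.** The inconsistency is real and should be fixed. Two current statements of the study's detection rule differ on whether an ECG is required for 2 of 4 pulse findings, with section 2.4 the less demanding in both. The count rests on applying 120 beats/min to the Abstract and on reading arrhythmia there as an irregular pulse.

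High confidence applies to this mismatch of wording only, not to any effect on conduct or results. If the sites used *or*, the harm is limited to an unclear rule in the Methods. If any site used the literal *and*, slower-rate AF could have gone unconfirmed there and the AF proportion could be too low, by an amount that the documents do not allow to be derived.

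**What to change.** 1. Check Figure 1 and ask the six hospitals which rule they have applied since September 2022.
2. Reword the trigger in section 2.4 to: an irregular pulse at any rate, or a heart rate of at least 120 beats/min. Keep the 12-lead ECG within 5 minutes for these pulse findings.
3. List chest symptoms in section 2.4 as a separate ECG trigger, as the Abstract does, without attaching the 5-minute limit. The Abstract sets no deadline for symptom-driven ECGs, and adding one would be a new requirement rather than a correction.
4. If any site used the *and* rule, switch its remaining checks to *or*, correct the Abstract's description of what was done, report the AF proportion under the rule actually used, and state as a limitation that slower-rate AF was not systematically tested.

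The cost is one short query to six sites and a small change of wording, with no new data field. The downside is that a site that switches late leaves data under two rules, which the report must say. The article appeared on 16 August 2023 and recruitment was due to end that month, so most past checks can no longer be changed, only described correctly.
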